**Fig. 1 Fig1:**
[figure not shown]
Anticipated participant recruitment flowchart

Group A will complete hearing assessment, cognitive, mental health and QoL assessment at the baseline, 6, 12, 18 and 24 months.

Group B will complete hearing assessment, cognitive, mental health and QoL assessment at the baseline, 6, 12 months, 18 and 24 months. (Primary endpoint analysis at 12 months and follow-up analysis at 24 months are shown in Fig. 1). Timeline of the study is shown in Table 1.

**Table 1 Tab1:**
[figure not shown]
Timeline of the study

**Intervention:** will be conducted by a qualified Audiologist.

**Part I: Hearing assessment and HA discussion**

During this appointment, the participant will complete (1) a comprehensive case history on their medical and hearing history, (2) a Client Oriented Scale of Improvement (COSI) goals [32] for everyday listening situations and (3) a standard hearing assessment. An explanation on what are hearing aids and how they work, what they are used for, how to use them, and related questions and answers will be provided.

**Part II:** HA fitting, real-ear verification and validation -immediately following appointment part I.

The audiologist will program the HA and carry out the real-ear verification using real-ear insertion gain (REIG) to ensure that appropriate amplification is provided validation tasks will be carried out to determine that the participant is benefitting from the HAs [33]. Adjustments will be made to the devices so that the participant is comfortable with the devices.

**Part III: HA review:** 2 weeks after the HA fitting.

HA data logging information recorded in the software of the HA is analysed to ensure that the HA program provides the best solutions to the listening demands of the participant. Based on COSI goals, data logging information and feedback received from the participants, changes are made to the HA program.

### HA review appointments at 12 and 24 months after HA fitting

These appointments are similar to Part II and III of the HA fitting appointments. During these appointments, a standard pure-tone audiometric assessment to obtain hearing thresholds, reprogramming of the HA according to the current hearing loss.

### Measuring adherence with treatment

The Oticon Opn 1S HAs have a “log in“feature that records both the average number of hours and different listening environments in which the participant has used the HA. These data can be retrieved when the HA is connected to the program software, which will be done at all assessments. In addition, the participant will be asked to maintain a daily listening diary in which s/he records the number of hours the HA is worn.

### Pilot test and sample size

In preparation of this trial, we conducted a pilot observational intervention study of two groups of hearing-impaired older adults: Group 1 [*n* = 35, mean age = 70.2 + 6.7 years, better ear four frequency average .5, 1, 2 & 4 kHz (BE 4PTA) = 31.92 dB, better ear high frequency average of 6 & 8 kHz (BE HF2PA) = 54.07 dB] and Group 2 [*n* = 13, mean age = 71.8 + 7.4 years, BE 4PTA = 33.46 dB, BE 2HFPTA = 55.57 dB]. A control group of 19 normal-hearing participants was also included. All participants completed hearing and a non-verbal cognitive assessment using the CANTAB test battery at baseline, 6 and 12 months. Hearing aids (HA) were fitted to Group 2 participants after the baseline assessment. Analysis of variance revealed that Group 2 participants (HA users) performed significantly better than Group 1 (non-HA users) on the delayed matching-to-sample (DMS) test of the CANTAB battery (*p* = .02, d = 0.38). We used G*Power software [34] to determine the required sample size for the study. Based on these pilot data, we calculated that a total of 140 participants would be required (70 in each group) to detect a conservative effect size of the intervention of d = 0.27 with two-sided α set at .05 and power of .90. To account for 25% of attrition over time, we estimated that a total of 180 participants would need to be recruited.

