#### Primary outcome measures

*Global cognitive abilities:* Due to hearing impairment, older people may experience difficulty in following verbal instructions or completing tasks that heavily rely on hearing during cognitive assessments. This may result in overestimation of cognitive impairment in such individuals [5]. Hence, we have used a non-verbal global cognitive measure that has been validated to use with the hearing impaired older adults. The global cognitive abilities will be measured using the Montreal Cognitive Assessment for the Hearing Impaired (HI- MoCA [11]. No significant difference was observed for MOCA and HI-MOCA scores in cognitively intact normal hearing participants, and the test-retest reliability coefficient was 0.66 [11].

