#### Secondary outcome measures

*Nonverbal cognition assessment using Cambridge Neuropsychological Test Battery (CANTAB)* [16]*- This assessment does NOT rely on verbal communication:*
Attention Switching task (AST): is a test of executive functioning and provides a measure of cued attentional set-shifting [16]. AST is based on the Stroop test and relies heavily on the functions of the anterior right hemisphere and medial frontal structures.Delayed Matching Sample (DMS): assesses participants’ ability to recognise complex visual patterns at different time intervals [16]. It is primarily sensitive to medial temporal lobe dysfunction.Paired Associates Learning (PAL): PAL is a recall test of memory which assesses episodic visuospatial memory, learning and association ability [16]. PAL is primarily sensitive to the changes in medial temporal lobe functioning.Spatial Working Memory (SWM): measures the retention and manipulation of visuospatial information in areas such as non-verbal working memory, working visuospatial memory and strategy use [16].

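### The stated 90% power is not supported for the primary outcome, HI-MoCA: its only basis is a pilot effect on a secondary test, and the stated inputs do not give 90% in a plain two-group comparison

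*Protocol article*

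**What the plan says.** All references are to the protocol article.

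- **Primary outcome** (Primary outcome measures): "The global cognitive abilities will be measured using the Montreal Cognitive Assessment for the Hearing Impaired (HI- MoCA". The text with Fig. 1 places the primary endpoint analysis at 12 months. The only numerical property given for HI-MoCA is a test-retest reliability of 0.66.
- **DMS** (Secondary outcome measures) is one of four CANTAB tests listed as secondary: "Delayed Matching Sample (DMS): assesses participants’ ability to recognise complex visual patterns at different time intervals".
- **Pilot** (Pilot test and sample size): "we conducted a pilot observational intervention study of two groups of hearing-impaired older adults". It had 35 non-users and 13 hearing-aid users, plus normal-hearing controls. The cognitive assessment described is CANTAB; HI-MoCA is not mentioned. One effect is reported: users "performed significantly better than Group 1 (non-HA users) on the delayed matching-to-sample (DMS) test of the CANTAB battery", with p = .02 and d = 0.38.
- **Sample size** (same section): "Based on these pilot data, we calculated that a total of 140 participants would be required", 70 per group, for d = 0.27 (called conservative), two-sided alpha .05 and power .90. Attrition of 25% brings recruitment to 180.
- **Analysis** (Statistical analysis): multilevel mixed models over time. No correlation between visits is given.

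**The concern.** The trial has one power statement. Its evidence is an effect on a test that the trial treats as secondary, in a small non-randomised comparison. Nothing in the section links 0.27 to HI-MoCA: there is no HI-MoCA standard deviation, no expected difference in points, no correlation, and no argument that an effect on DMS should carry over to a global screening score. The step from 0.38 to 0.27 is not explained either.

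Readers will take 90% as the chance of detecting a real HI-MoCA benefit. A null HI-MoCA result could then be read as good evidence of no benefit, although power for that outcome was never established. The Discussion expects the results to move quickly into audiology practice, so the reading of a null result matters.

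**Working it through.** **Inputs from the article:** d = 0.27, two-sided alpha 0.05, power 0.90, 70 per group; pilot d = 0.38 with p = .02 and n = 35 and 13; attrition 25%; 180 recruited. **Assumptions of this check:** a baseline-to-12-month correlation of 0.66, which borrows the stated test-retest reliability, and HI-MoCA SDs of 2, 3 and 4 points. The article gives neither quantity.

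1. **The plan's own figure.** For two independent groups, n per arm = 2(1.960 + 1.282)² / 0.27² = 2 × 10.507 / 0.0729 = 288.3, so 289 per arm (290 by the exact t distribution). The total is 578, against the stated 140. The figure is not reproduced.

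2. **Power delivered by 70 per arm at d = 0.27.** SE = √(2/70) = 0.169; 0.27/0.169 = 1.597; power = Φ(1.597 − 1.960) = 36%. The unreduced pilot value of 0.38 would give 61%.

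3. **With baseline adjustment at r = 0.66.** The residual SD factor is √(1 − 0.66²) = 0.751. Then 0.27/0.751 = 0.359; 0.359/0.169 = 2.126; power = Φ(2.126 − 1.960) = 57%, and 90% power needs 164 per arm. To reach 90% with 70 per arm, r would have to be about 0.87.

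4. **Effect detectable with 90% power at 70 per arm.** 3.242 × 0.169 = 0.55 SD unadjusted; 0.548 × 0.751 = 0.41 SD adjusted. These hold for any outcome, DMS included. In HI-MoCA points:

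| Assumed SD | 0.27 SD | 0.548 SD (unadjusted) | 0.412 SD (adjusted, r = 0.66) |
|---|---|---|---|
| 2 | 0.5 | 1.1 | 0.8 |
| 3 | 0.8 | 1.6 | 1.2 |
| 4 | 1.1 | 2.2 | 1.6 |

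5. **Readings that come near 140.**
   - If 0.27 is Cohen's f, d = 0.54, the total is 146 to 148, and power at 140 is 0.89.
   - A repeated-measures group-by-time F test with f = 0.27/2 = 0.135 gives about 140 if the correlation between visits is about 0.53 with 2 visits, 0.40 with 3, or 0.19 with 5. No such correlation is stated.

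6. **Consistency of the pilot effect.** As a plain two-group d, t = 0.38 × √(35 × 13/48) = 1.17 on 46 df, so p is about 0.25, not .02. The 95% interval is 0.38 ± 1.96 × 0.327, or −0.26 to 1.02. A two-group p of .02 would need d of about 0.78. If 0.38 were Cohen's f, F = 0.38² × 46 = 6.64 and p is about 0.013. The reported pair therefore does not fit a plain d and is closer to f. The pilot ANOVA is not described, so this is an indication only.

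7. **Evaluable number.** 180 × 0.75 = 135, below 140 (140/0.75 = 187). With 67.5 per arm, power for d = 0.27 is 35% unadjusted. Adjusted at r = 0.66 it is Φ(0.359/√(2/67.5) − 1.960) = 55%.

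8. **HI-MoCA itself.** No specific power can be computed, because the article gives no HI-MoCA SD, difference or correlation. Steps 2 to 4 show only what the design delivers for a given standardised effect.

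**The case against.** The strongest reply is that a standardised effect belongs to no particular scale. The section does not say that the sample size was calculated for DMS. It gives a reduced effect of the intervention (0.38 cut to 0.27, about 29%) without naming an outcome. If the true HI-MoCA effect were 0.27, power for 0.27 would apply to HI-MoCA. This stands. A reader might infer that the calculation was done for DMS and cannot apply to HI-MoCA, but the text does not support that. What it shows is that nothing in it justifies 0.27 for HI-MoCA.

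Four other inferences should also be resisted:

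- **That HI-MoCA, with reliability 0.66, is a weaker measure than DMS.** No DMS reliability is given, so there is no comparison.
- **That DMS was picked because it was the significant test.** The results of the other CANTAB tests and the way DMS was chosen are not reported.
- **That the pilot participants were cognitively unlike the trial's.** The short description gives no cognitive criterion, and a condensed article may omit one.
- **That the trial has 36% power.** That is the result for a plain comparison at d = 0.27. The planned mixed model uses baseline and a 6-month visit and would do better to an extent that depends on the unstated correlation. The value 0.66 is borrowed, and restricting entry to HI-MoCA scores of 19 to 25 would tend to lower the correlation.

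It can also be said that an article condenses, and that an SD or correlation may sit in the full protocol. But the article does publish its basis for the sample size. The objection is to what that basis says, which rests on an outcome other than the primary one and gives inputs that do not produce the stated number.

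**Conclusion.** The concern holds in this form: the 90% power is not supported for HI-MoCA. Its only evidence is one DMS effect from 13 users and 35 non-users in an observational pilot, reduced without explanation to a value tied to no outcome. Separately, the stated inputs do not give 90% for any outcome in a plain two-group comparison: about 36% at 70 per arm, or about 57% adjusted under the assumed correlation of 0.66, with 0.55 SD or 0.41 SD needed for 90%. The gap nearly closes if 0.27 is Cohen's f, or if a suitable repeated-measures correlation was used; the article states neither. Even then no HI-MoCA input would be supplied. The conflict between d = 0.38 and p = .02 means that the effect metric must be clarified in any case.

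The textual facts are firm. The figures in points depend wholly on the assumed SDs.

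**What to change.** Restate the power paragraph for the 12-month HI-MoCA contrast under the planned mixed model. It should give:

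- the effect-size metric (d or f) and the test family used in the software;
- the assumed HI-MoCA SD and correlation between visits, labelled as assumptions and shown over a range;
- the target difference in HI-MoCA points;
- the power delivered by the expected evaluable number, 135 after 25% attrition from 180.

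Cite the DMS pilot only as background from a non-randomised study on a secondary outcome, and explain the step from 0.38 to 0.27 if it is still used. Do not carry over the 90% figure unless it can be reproduced from stated inputs.

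The cost is a recalculation and revised wording in the protocol or SAP. Enrolment is unchanged. The drawback is a stated power that is probably less favourable.

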**Methods:**

The HearCog trial is a 24-month, randomised, controlled clinical trial aimed at determining whether a hearing loss intervention can delay or arrest the cognitive decline. We will randomise 180 older adults with hearing loss and mild cognitive impairment to a hearing aid or control group to determine if the fitting of hearing aids decreases the 12-month rate of cognitive decline compared with the control group. In addition, we will also determine if the expected clinical gains achieved after 12 months can be sustained over an additional 12 months and if losses experienced through the non-correction of hearing loss can be reversed with the fitting of hearing aids after 12 months.

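### Recruiting 180 does not cover 25% attrition: it leaves 135, below the required 140, which would need 187 recruits

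*Protocol article*

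**What the plan says.** All the figures are in two consecutive sentences of the Protocol article, section Pilot test and sample size. The first says that "a total of 140 participants would be required (70 in each group"), with "two-sided α set at .05 and power of .90", "to detect a conservative effect size of the intervention of d = 0.27". The second adds the allowance for loss: "To account for 25% of attrition over time, we estimated that a total of 180 participants would need to be recruited".

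The total of 180 is repeated in the Abstract ("We will randomise 180 older adults with hearing loss and mild cognitive impairment") and under Participants and setting. These places only restate the total and contain no separate error. The article gives no other allowance, and no definition of attrition that would lead from 140 to 180.

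**The concern.** The second sentence presents 180 as the number that protects the required 140 against a 25% loss. To keep a target after losing a fraction d, the target is divided by 1 − d. Here that gives a figure above 180, so the plan's own retention assumption breaks its own target.

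What is at stake is the sample-size justification. A reader would take it that the trial can lose a quarter of its participants and still have the number it says it needs. On the stated figures it cannot. The Statistical analysis section also brings in imputation only when loss exceeds 25%, so losses between 22.2% and 25% would miss the target without reaching that trigger.

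**Working it through.** **Inputs** (all from Pilot test and sample size)
- Required number: 140, as "70 in each group"
- Attrition: 25%
- Recruitment total: 180

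**Trying to reproduce 180**
- Division by the retained fraction: 140/(1 − 0.25) = 186.7, so 187. By arm: 70/0.75 = 93.3, so 94 per arm and 188 in total.
- Multiplicative shortcut, which does not protect the target: 140 × 1.25 = 175.
- The factor actually used: 180/140 = 1.286. The correct factor is 1/0.75 = 1.333 and the shortcut factor is 1.25.

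Neither formula gives 180. The nearest route is the shortcut's 175 rounded up by 5. The document does not say how 180 was reached.

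**Working forward from 180**
- Expected number remaining: 180 × 0.75 = 135, or 67.5 per arm.
- Shortfall: 140 − 135 = 5, which is 3.6% of 140.
- Largest loss that still leaves 140: 1 − 140/180 = 22.2%.
- If each participant independently has a 25% chance of being lost, the chance that at least 140 of 180 remain is P(Bin(180, 0.75) ≥ 140) = 0.221. The target would be missed about 78% of the time, usually by a few participants.

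**Effect on power**

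Take the plan's 90% power at 140 as given. Going to 135 multiplies the noncentrality by √(135/140) = 0.982. For two-sided α = 0.05 the noncentrality at 90% power is 1.960 + 1.282 = 3.242. This becomes 3.242 × 0.982 = 3.183, and power is Φ(3.183 − 1.960) = 0.889. The loss is about 1 percentage point.

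The size of that loss hardly depends on how 140 was obtained:

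| Two-sample t-test | Power, 70 per arm | Power, 67.5 per arm |
|---|---|---|
| d = 0.27 | 0.354 | 0.344 |
| d = 0.54 (0.27 read as Cohen's f) | 0.887 | 0.876 |

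**The case against.** The strongest reply is that the consequence depends on things the article leaves open.

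- **Time point.** The 25% is described only as occurring over time. Follow-up lasts 24 months, but the primary endpoint analysis is at 12. If 25% is the 24-month figure, fewer would be lost by month 12. As an illustration, a constant dropout rate gives 1 − √0.75 = 13.4% at 12 months, leaving about 156 of 180, which is above 140. This stands as a limit on the consequence: a shortfall at the primary endpoint is not established. It does not rescue the sentence, which ties 25% to 180 without naming a time point.
- **Partial data.** The analysis uses mixed models with visits at baseline, 6, 12, 18 and 24 months, so someone lost after month 6 still contributes. Counting every dropout as a complete loss is a worst case. This also stands, but the sample-size section does not use the argument and shows no calculation based on it.
- **Rounding.** The text says the total was estimated, and 180 could be 175 rounded up. That may explain where the number came from, but 175 is itself the result of the wrong formula.
- **Size.** Five participants and about one point of power is little. That is accepted. The 22% chance of keeping 140 is correct, but it measures whether a threshold is crossed and should be read alongside the power figure.

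**Conclusion.** The concern holds. A required 140, an attrition of 25% and a recruitment total of 180 cannot all be right: 180 leaves 135, and 140 needs 187 (188 with equal arms). As arithmetic, this rests only on the three stated figures.

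The consequence is minor. The expected shortfall is 5 participants and about 1 point of power, assuming that the 25% applies at the 12-month analysis and that dropouts contribute no data. If either assumption fails, the loss is smaller or absent.

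This verdict concerns the inflation step alone and does not endorse the 140. A plain two-group comparison at d = 0.27, two-sided α = 0.05 and 90% power needs 289 per arm, and 70 per arm gives about 35% power. The method behind 140 is a separate and larger question. Whatever base number results from it, the attrition allowance has to be applied by division.

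**What to change.** Correct the attrition sentence in Pilot test and sample size in one of two ways.

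1. Keep 180 and give the allowance as 22%. Check: 180 × 0.78 = 140.4.
2. Keep 25% and state that 135 participants (67 to 68 per arm) are expected to remain, with the power statement based on that number. This requires the method behind 140 to be stated first, because the power at 67 to 68 per arm cannot be given without it.

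In either case, state whether the allowance refers to month 12 (the primary endpoint) or month 24. If dropouts are expected to contribute through the mixed model, say so.

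The cost is one sentence and a slightly less favourable stated figure, with no change to design, conduct or enrolment. Keeping both 140 and 25% is also consistent, but it means recruiting 188 in equal arms, 8 more than planned. For a gain of about one point of power, that is not needed to put the text right.

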### Randomisation, concealment and blinding

The computer-generated randomisation sequence will be stratified by the severity of the hearing loss (mild to moderate vs severe) based on the results of the hearing assessment. Each stratification block will be associated with a random sequence of numbers assigned to the intervention and control group in random permuted blocks of 6, 8 or 10. This sequence will be stored in a password-protected server housed at the University of Western Australia and will be managed by a biostatistician not involved in this project. Once a participant consents and is enrolled, s/he will be automatically ascribed a number and group membership (intervention or control).

Due to the nature of the intervention, participants will know their group assignment, but research staff involved in the assessment of cognitive function, quality of life, mood and physical function will remain blind to treatment allocation. This will be achieved by directing participants to **NOT**: (i) discuss any aspects of the intervention during the assessments, (ii) wear their HAs during the assessment. Binaural hearing amplifiers will be used to facilitate the communication between participants and research staff during all assessment visits (including the 12 and 24-month visits).

### Health economic analysis

This will involve the development of a model to estimate the incremental cost-effectiveness of the intervention compared to the control. The analyses will be from the perspective of the health service and will be expressed as Quality-Adjusted Life Years gained. A particular focus of the economic evaluation will be a full assessment of the cost of delivering the intervention compared to that of the control group (including the costs of intervention material, costs of procedures, visits to health service provides and list of all medications). Given the feasibility of obtaining health administrative data within the study time frame, we will use a validated patient cost questionnaire to obtain self-reported health care utilisation data [35]. Whilst we recognise the potential for recall bias, there is evidence to suggest that this is a valid method of collecting data on health-care resource utilisation for use in economic evaluations, especially when administrative data is not easily available [36]. Costings information will be applied based on established economic costing methodologies drawing on primary research and secondary national tariffs [37]. Further, an application will be made to the Department of Health Linked data systems obtain pharmaceutical-based costs, Medicare-based costs and other associated costs including Mental Health Information System, Home and Community Care, Emergency Department Data, Aged Care Assessment and St John Ambulance related to each participant of the study.

The second aspect will include the assessment of the effectiveness of the intervention – effectiveness of the intervention and control will be measured using the SF-12, which is widely used in economic evaluations.

Incremental cost-effectiveness ratios will be calculated in terms of the incremental cost per sustained remission and the incremental cost per Quality-Adjusted Life Year (QALY) gained by the intervention. The QALY is a widely-used approach for estimating the quality of life benefits in economic evaluations. The values obtained from the SF-12 will be transformed into utility weights using the Short Form 6D algorithm [38] to formulate the cost per QALY. Sensitivity analysis will be undertaken to test the robustness of results.

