## Methods

### Aims

This trial will determine whether the correction of hearing loss through the use of hearing aids (HA) decreases the 12-month rate of cognitive decline among older adults at risk of dementia.We will also investigate whether the correction of hearing loss has a beneficial impact on memory and executive functions, anxiety and depressive symptoms, quality of life, physical health, and health-related costs over 12 months.We will explore whether the expected clinical gains achieved through the correction of hearing loss by 12 months can be sustained over an additional period of 12 months and if losses experienced through the non-correction of hearing loss can be reversed with the fitting of HAs after 12 months (i.e., HAs fitting for controls at 12 months with follow up of 12 months).

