## Discussion

The current paper discusses the methodology for a randomised control trial that investigates whether hearing loss intervention using hearing aids could delay or arrest the cognitive decline in older adults with mild cognitive impairment. One of the strengths of this trial is that it follows CONSORT guidelines for the design of randomised controlled trials. The recruitment of participants with mild cognitive deficits was guided by our desire to test a population at risk of dementia (when prevention may be possible) and by the difficulties associated with the consenting of older adults with moderate to severe cognitive impairment. Besides, those with severe to profound hearing loss who meet the criteria for a cochlear implant will not benefit from HA amplification, hence, including them would potentially undermine the impact of HA amplification on cognitive functions, mental health and QoL. We acknowledge, however, that our study will focus on the cognitive decline rather than conversion to dementia. At this stage, this is a “proof of concept’ investigation, as a dementia prevention trial would require a substantially larger sample and follow up. The projected outcomes of the current study can immediately be translated to practice through audiology clinics and will be applicable across practices around the world. Findings can also be used to inform audiologists, general practitioners and other health-care providers. This will provide important information for older people about the use of hearing aids to prevent worsening cognitive impairment. In addition, consumer support will be requested in disseminating lay summaries/information to the community. If cognitive decline can be delayed or arrested, this would improve the quality of life of older adults who are at risk of developing dementia. It may also lower costs to the health-care and social support systems, by decreasing the needs for services and residential care placement. It would also significantly reduce the overall burden borne by the community.

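### One of the two planned cost-effectiveness ratios is a cost per sustained remission, which matches no aim, entry criterion, outcome or analysis in this trial

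*Protocol article*

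**What the plan says.** The Health economic analysis section of the protocol article commits to two ratios. The first: "Incremental cost-effectiveness ratios will be calculated in terms of the incremental cost per sustained remission". The second is "the incremental cost per Quality-Adjusted Life Year (QALY) gained by the intervention". Earlier in the same section the results "will be expressed as Quality-Adjusted Life Years gained", and the section also says that "effectiveness of the intervention and control will be measured using the SF-12", with SF-12 responses converted to utilities by the SF-6D algorithm.

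Elsewhere, the Aims section asks whether hearing aids "decreases the 12-month rate of cognitive decline among older adults at risk of dementia". Under Primary outcome measures, "The global cognitive abilities will be measured using the Montreal Cognitive Assessment for the Hearing Impaired". The Discussion adds that "our study will focus on the cognitive decline rather than conversion to dementia".

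**The concern.** An incremental cost-effectiveness ratio needs an effect that the trial can count in each arm. Remission presupposes an illness state that is present at entry and can clear. This trial recruits people with hearing loss and mildly reduced cognition and asks whether decline is slower with hearing aids. The remission ratio looks out of place in that design, and the article gives nothing from which to build it.

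At stake is one economic result. If the wording stands, the team must either leave a published analysis undone or supply an endpoint of its own. Several scales, each measured at five visits, would offer many candidates for that endpoint. The ratio would also not express cost against the effect that the trial was set up to estimate.

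**Working it through.** No arithmetic applies, and the plan gives no figure to reproduce. The check is to write down what each ratio needs and to look for it in the rest of the article.

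**What the ratios need.** Each has the form (mean cost in Group A − mean cost in Group B) ÷ (effect in Group A − effect in Group B).
- For cost per QALY, the effect is mean QALYs per arm. The article gives the instrument (SF-12) and the conversion (SF-6D). This ratio can be formed.
- For cost per sustained remission, the effect is the number or proportion of participants in sustained remission per arm. That requires a condition, an instrument, a threshold and a duration.

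**Where those four items might be found.**

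| Section | Content | Supplies a remission state? |
|---|---|---|
| Aims | Rate of cognitive decline over 12 months; effects on memory, executive function, mood, quality of life, physical health and costs; durability of gains to 24 months; reversal of losses in controls once fitted | No |
| Eligibility criteria | Age 70 or over, HI-MoCA above 18 and below 26, hearing loss, fluent English | No; no depressive, anxiety or other episode is required |
| Primary outcome measures | HI-MoCA score | No |
| Secondary outcome measures | Four CANTAB tests | No |
| Other measures | Among others PHQ-9, GAI, SF-12, IADL and HHIE | Symptom and function scales; no remission cut-off given |
| Statistical analysis | Mixed models of change in scale scores | No responder or remission analysis |
| Discussion | Delaying or arresting decline | No |
| Health economic analysis | QALYs, SF-12, SF-6D | Supports the second ratio only |

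The term remission occurs once in the article, in the sentence at issue. Fig. 1 and Table 1 are not reproduced in the text at hand, but their captions describe a recruitment flowchart and a timeline and give no sign of a remission definition.

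**The nearest candidates.** The Aims ask whether gains "can be sustained over an additional period of 12 months". That is maintenance of a benefit from month 12 to month 24, not clearing of an illness. The Aims also ask whether losses in controls can be reversed after they are fitted. That concerns recovery within Group B after it has received the intervention, so it does not supply a between-arm difference in remissions.

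**Result.** None of the four items is supplied, and the only related wording describes something else. Of the two stated ratios, one can be formed from the plan and one cannot.

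**The case against.** The strongest reply is that a journal article condenses a fuller protocol, and that the operational definition of an economic endpoint normally sits in the analysis plan or the economic plan. That is fair, and the absence of a definition alone would not be a finding. What survives is the mismatch: the article positively names an endpoint that does not fit its own population, aims, outcomes or analysis and sits beside a statement that results are expressed in QALYs. An analysis plan elaborates a stated endpoint; here it would have to introduce one.

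The other side is also right that several stronger readings are not supported:

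- *That the ratio is impossible under any definition.* A binary state could be derived from the repeated PHQ-9, GAI or HI-MoCA scores, since cognition and mental health are assessed at baseline and at 6, 12, 18 and 24 months. The article defines no such state and requires no depression or anxiety at entry, so the accurate statement is that the ratio cannot be formed as specified.
- *That any later definition would be post hoc.* A definition fixed before outcome data are analysed would be prespecified, wherever it was recorded.
- *That a 24-month economic comparison is spoiled because controls are fitted at month 12.* The economic section states no 24-month horizon. The Aims place health-related costs over 12 months, and the primary endpoint analysis is at 12 months.
- *That a HI-MoCA of 26 or more, used as remission, would mostly pick up measurement error.* The article proposes no such cut-off. Its test-retest coefficient of 0.66 is reported alongside a comparison in cognitively intact people with normal hearing, and no standard deviation is given, so the share due to error cannot be worked out. Regression to the mean would also be expected in both arms.

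Finally, the Abstract says only that cost-effectiveness will be explored, which limits how much weight this error carries.

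**Conclusion.** The sentence is wrong as written, and the severity is minor. One of the two stated cost-effectiveness ratios has a denominator that matches no stated aim or outcome and cannot be formed as specified. The cost-per-QALY ratio, the primary analysis, the secondary outcomes and the sample size are unaffected. A reader might infer that the economic evaluation as a whole fails; it does not, because the QALY route is set out.

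The conclusion assumes that the unseen full protocol and analysis plan do not give remission a meaning in this trial. If one of them does, the missing definition is settled, but the article's aims and outcomes would still not match the ratio and would need to be reconciled with it.

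**What to change.** Before outcome data are examined, make one of two changes in the Health economic analysis section and in any economic or statistical analysis plan that repeats the sentence:

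1. **Replace** the remission ratio with incremental cost per HI-MoCA point of decline averted at 12 months. The numerator is the between-arm difference in mean cost over 12 months; the denominator is the between-arm difference in mean HI-MoCA change from baseline to 12 months, signed so that less decline counts as benefit. This ties the ratio to the primary outcome and endpoint and matches the 12-month frame that the Aims give for costs.
2. **Delete** the remission ratio and keep cost per QALY only, in line with the rest of the section.

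Nothing in the article requires a ratio on the primary outcome, so the choice is the sponsor's. The cost is a clause deleted or a sentence replaced. HI-MoCA, SF-12 and self-reported health-care use are already to be collected, so no new data or visits are needed. The change should be dated, to show that it preceded the analysis.
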